**Abstract**

Traumatic events, such as traffic accidents, assaults and rapes, are unfortunately common phenomena in the population. Typical reactions for victims are flashbacks, increased anxiety and depressive symptoms. These symptoms usually disappear within a few months after the event, but for about 20%, these symptoms may develop into post-traumatic stress disorder (PTSD).

Although PTSD is relatively common, only a fraction of sufferers are detected by the health care system and detected cases are often left without proper treatment. PTSD is associated with increased risk of suicide and sick leave, and preventive work is clearly needed to lower the incidence of this disorder. Critically, as PTSD is the only mental health disorder where we have a known onset event, we should seize the opportunity to prevent the buildup of potentially long-standing symptoms.

Trauma Focused Cognitive-Behavior Therapy (TF-CBT) is the most promising intervention for preventing PTSD. TF-CBT is provided directly at the hospital emergency room, and has been shown in one trial to decrease the incidence of later PTSD. However, this recent and promising study acknowledged several limitations such as a small sample size, short follow-up time and lack of proper monitoring of treatment side effects.

In light of this, we propose a large-scale randomized trial (n=352), where patients attending an emergency room and have experienced a traumatic event are randomized to either TF-CBT or treatment-as-usual. We will measure PTSD symptoms, quality of life, treatment side effects, process data as well as health economic data up to 10 years.

If TF-CBT is found to be effective, it would mean that we can intervene on PTSD before it develops and we would have valuable knowledge about it´s cost-effectiveness and on the biological and psychological mechanisms that are at play. This would be of immense importance to the millions of people worldwide who will experience inevitable future accidents and traumatic events.

Introduction

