2.2.1 IS TF-CBT AN EFFICATIOUS AND SAFE TREATMENT IN PREVENTING PTSD?

One major limitation with the Rothbaum et al. trial was that it used a relatively small sample size (n=137) and this may question the reliability of the results. It is important to note that in these settings a sizeable portion of the participants will recover spontaneously and larger samples are needed as compared to treatments of chronic patients. Another limitation in their study was the short follow-up time of 12 weeks. This is problematic both from a scientific view as well as for policy makers because we do not know how this treatment stands in a 6- or 12-month period. Furthermore, the Rothbaum study also lacked systematic data collection on potential side effects that were associated with the treatment. This is an important issue as one psychological intervention for PTSD (i.e. “Debriefing”) has actually shown worsening of symptoms compared to treatment-as-usual.[^17^](#_ENREF_17) Thus, we need to do a large-scale trial with longer follow-up assessments and close monitoring of adverse events .

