Participants randomized to TF-CBT will receive a brief 3-session intervention provided within 72 hours after the accident. In this treatment, the patient is instructed to systematically expose him/herself to the fearful memory of the event and stay in this memory until the anxiety has attenuated. By doing this exposure repeated times, the association between the memory and fear response is hypothesized to be gradually extinguished. The placebo group will receive sham treatment i.e. written information about PTSD and how to treat it but without any therapist-guided interventions.

We will measure PTSD symptoms using the Clinician Administered PTSD Scale (CAPS; the gold standard for PTSD assessment) and Posttraumatic Diagnostic Scale,[^22^](#_ENREF_22)^,^[^23^](#_ENREF_23) depression using the Montgomery Åsberg Depression Rating Scale – Self rated (MADRS-S),[^24^](#_ENREF_24) quality of life using the EQ-5D[^25^](#_ENREF_25) and treatment side effects using the Safety Monitoring Uniform Report Form (SMURF)[^26^](#_ENREF_26) at baseline (i.e. before treatment allocation), 2-, 6-, 12-, 24-, 48- and 120 months using blinded assessors. Primary endpoint is set to 6-months after the trauma. Patients unable to come to the clinic for follow-up assessments will be interviewed via telephone or skype.

The primary outcome (significant PTSD symptoms assessed by the CAPS) will be analyzed using risk ratios and numbers-needed-to-treat with 95% confidence intervals. Continuous data will be analyzed in a mixed-effects model adjusting for data attrition (covariance and residual structure will be set based on the best model fit of the data) using intention-to-treat design. Effect sizes for continuous measures will be estimated using Cohen´s *d*. Assessor´s blindness will be also tested (each assessor will guess treatment allocation for each participant and this will be tested in a logistic regression with guess as independent variable and allocation as dependent variable). A flowchart of the treatment study is shown in the attached figure.

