**2 IS TF-CBT A COST-EFFECTIVE TREATMENT IN PREVENTING THE DEVELOPMENT OF PTSD SYMPTOMS?**

2.1 OVERALL DESIGN

Patients from the randomized trial (research question 1) will be followed in the patient register (Patientregistret), the prescription register (Läkemedelsregistret) and the longitudinal integrated data-base for health insurance and work-related research (LISA - Longitudinell integrationsdatabas för sjukförsäkrings-och arbetsmarknadsstudier) Costs will be analyzed using a societal perspective i.e. including both sick leave, hospitalizations, medical use etc. and analyzed in relation to outcome (i.e. PTSD symptoms and also quality-adjusted life years which are assessed in the randomized trial using the CAPS and EQ-5D).

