2.3 COST-EFFECTIVENESS ANALYSES

Cost-effectiveness comparisons will be analyzed using incremental cost-effectiveness ratios as well as the net benefit approach with different willingness-to-pay scenarios. Cost-effectiveness ratios are calculated as following: (Δ^C1^ – Δ^C2^)/(Δ^E1^ – Δ^E2^), where Δ^C1^ – Δ^C2^ is the difference in cost change (from pre- to follow-up) between the two treatment groups. Δ^E1^ – Δ^E2^ refers to the corresponding difference in clinical outcome (i.e. PTSD vs. no PTSD). Because cost-effectiveness is a relative term i.e. an intervention is only cost-effective depending on how much the society is willing to pay for one unit of improvement, we will also use the ”net benefit approach”, which estimates the cost-effectiveness depending on different societal willingness-to-pay values for one unit of improvement. The net benefit of each individual in this trial will be calculated according to the following formula: (λ x E) – Δ^C^ where λ is the willingness to pay (i.e. the different values that the society is willing to pay for one unit of improvement), E is the efficacy (i.e. PTSD status or gain on the EQ-5D), and Δ^C^ is the cost change from baseline to primary endpoint (6-months). We will calculate individual net benefits by assuming different values for λ and a regression model with non-parametric bootstrapping (one thousand replications) to estimate be difference between TF-CBT treatment-as-usual. Cost-effectiveness acceptability curves will be used to get a visual estimate of the total net benefit of TF-CBT.

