# Societal implications

In the last decade, both the Swedish Government and the National Board of Health have underscored the importance of using a preventive health care approach.[^32^](#_ENREF_32)^,^[^33^](#_ENREF_33) PTSD is a major public health concern with long-term sequelae, and given the signiﬁcant public health impact of PTSD, there is a need for research on brief and cost-effective interventions that are easy to disseminate.

If TF-CBT would be shown effective, it would mean that the health care system could access and implement a new and brief intervention to the treatment armament and potentially “vaccinate” many trauma patients from developing PTSD. The cost-effectiveness aspect of the study will also provide us with important data whether TF-CBT also can decrease the burden on the social welfare system as well as psychiatry and addiction care. Thus, this project also holds important precision prevention features, similar to what has been done in cancer-, heart disease- or diabetes- research,[^12^](#_ENREF_12)^,^[^13^](#_ENREF_13) moving this for the first time in Sweden to psychological treatment research and mental health. Lastly, the data from the mediation analysis would provide us with better knowledge what to focus on in psychological treatment, hence potentially improve these interventions and thereby minimize treatment failures for many patients.

The prospect of being able to prevent PTSD by means of a psychological intervention poses great challenges, but the rewards are of immense importance: not only to the thousands of people in Sweden who every year are victims of road traffic accidents or interpersonal violence, but also to the millions of people worldwide who will experience inevitable future traumatic events.

Collaborations:

**[name]**, associate professor at Emory University Atlanta USA, is an external consultant in the current project. [name] is one of the top leading researchers on translational models of fear extinction, and was also one of the main authors behind the previous RCT on TF-CBT conducted in Atlanta, USA.[^16^](#_ENREF_16) We have previously worked with [name] in a randomized pharmacotrial with great success. More info at <[name]>. [name] will serve the function as an external consultant in the current project.

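### Six months, stated for costs only, is the only horizon fixed for the net-benefit analysis, although later EQ-5D visits and register costs are already planned

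*Protocol*

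**What the plan says.** Methods 2.3 plans two economic analyses.

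- **Net benefit.** Each patient's value is willingness to pay times effect, minus cost change. The cost change "is the cost change from baseline to primary endpoint (6-months"). The effect is described only as "E is the efficacy (i.e. PTSD status or gain on the EQ-5D"), with no time point. The bootstrapped regression uses these individual values, and acceptability curves are to display the total net benefit.
- **ICER.** The numerator "is the difference in cost change (from pre- to follow-up) between the two treatment groups"; which follow-up is meant is not stated. The effect is PTSD versus no PTSD.

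The data planned elsewhere run much further. Methods 1.1 schedules CAPS and EQ-5D "at baseline (i.e. before treatment allocation), 2-, 6-, 12-, 24-, 48- and 120 months using blinded assessors". Under Methods 2.1 patients "will be followed in the patient register (Patientregistret), the prescription register" and a third database on health insurance and work, from a societal perspective that includes sick leave, with no 6-month limit. The Abstract promises "process data as well as health economic data up to 10 years".

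**The concern.** Methods 2.2 counts the cost of an emergency-department psychologist as the treatment cost, and Methods 1.1 places the three sessions within 72 hours of the accident. That cost is therefore complete almost at once. The return on it (fewer cases, better quality of life, less sick leave and care) builds up for as long as prevention lasts. A window closing at 6 months takes in all of the first and truncates the second.

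This sits badly with the protocol's own aims. Introduction 2.2.1 faults the earlier trial's 12-week follow-up, also from the policy maker's side, because "we do not know how this treatment stands in a 6- or 12-month period". The net-benefit analysis as written never reaches 12 months. The Societal implications section expects the economic work to show "whether TF-CBT also can decrease the burden on the social welfare system as well as psychiatry and addiction care", and 6 months of cost is a thin basis for that. At stake is how well the trial can answer research question 2 from data it already intends to collect.

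There is a second, smaller problem. With the effect undated and the ICER's follow-up open, a 6-month cost could be paired with an effect from another visit.

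**Working it through.** The plan gives no figure for the share of cost or benefit inside the window, so there is none to reproduce. The sample size of 352 plays no part here.

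**Inputs from the protocol**
- Net-benefit cost horizon: 6 months (Methods 2.3).
- Later EQ-5D visits: 12, 24, 48 and 120 months (Methods 1.1).
- Treatment delivery: within 72 hours (Methods 1.1), so 100% of its cost lies inside 6 months.
- PTSD is defined as present at least one month after the event (Introduction 1.1). This motivates starting the gain at month 1.

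**Assumptions, not in the protocol**
- The gain starts at month 1 and decays exponentially with half-life h years.
- QALYs are discounted at 3% per year.

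**Step 1: calendar share of the window.** 6/24 = 25% of the time to the 24-month visit, 6/48 = 12.5% of the time to 48 months, and 6/120 = 5% of the time to 120 months.

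**Step 2: share of the accumulated QALY gain captured by 6 months.** With k = ln 2 / h + ln 1.03 (first term zero if there is no decay), and times in years,

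share(T) = [1 − exp(−k(0.5 − 1/12))] / [1 − exp(−k(T − 1/12))].

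The number of cases prevented and the utility loss per case multiply numerator and denominator alike and cancel. The share depends only on persistence and discounting.

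Example, no decay, T = 2: k = 0.02956. The numerator is 1 − exp(−0.0123) = 0.01224 and the denominator is 1 − exp(−0.0567) = 0.0551, giving 0.222.

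Example, h = 1, T = 2: k = 0.7227. The numerator is 0.260 and the denominator is 0.750, giving 0.347.

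| Assumed half-life | vs 12 months | vs 24 months | vs 48 months | vs 120 months |
|---|---|---|---|---|
| No decay | 46% | 22% | 11% | 5% |
| 5 years | 47% | 25% | 14% | 8% |
| 2 years | 50% | 28% | 19% | 15% |
| 1 year | 54% | 35% | 28% | 26% |
| 6 months | 61% | 48% | 45% | 45% |
| 3 months | 75% | 69% | 69% | 69% |

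Against 24 months, the window captures less than half of the gain once the half-life is about 6 months or longer, and more than half at 3 months.

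**Step 3: absolute size, for illustration.** Assume 5 to 10 percentage points fewer cases and a utility loss of 0.1 to 0.2 per case; neither range comes from the protocol. With no decay, the gain per patient is 0.0021 to 0.0083 QALY at 6 months and 0.0093 to 0.0372 at 24 months. With a 6-month half-life, it is 0.0016 to 0.0063 and 0.0033 to 0.0132.

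**Step 4: feasibility.** The time plan puts recruitment in 2016-2017 and follow-up in 2017-2019. A patient recruited at the end of 2017 reaches 24 months at the end of 2019, so both the 12- and 24-month visits fit.

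**The case against.** A 6-month analysis matched to the primary endpoint is legitimate, and listing further time points for the same regression is commonly left to an analysis plan that is not shown here. The first part stands: 6 months should stay. The second carries less weight, because the protocol does not leave the net-benefit horizon open. It writes one into the formula, and that horizon fits poorly with its stated aims. The time plan does place long-term assessments from 2020 outside the application, but it does not offer this as a reason for the 6-month cost limit, and 24 months falls within the planned period.

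A reader might go further in four ways that the documents do not support.

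- *The window cuts off most of the benefit.* No persistence of effect is given. The protocol itself says that symptoms usually subside within months and that many patients recover spontaneously, which could narrow the gap between arms. With a 3-month half-life, 6 months already holds 69% of the 24-month gain.
- *Cost per effect halves at 12 months and quarters at 24.* That holds only for accumulated QALYs with a constant effect from day one, no discounting and no offsets. It does not apply to PTSD status or to a change score on the EQ-5D, which is how Methods 2.3 words the effect.
- *The whole economic evaluation stops at 6 months, so research question 2 could be answered negatively for that reason alone.* The ICER and the register follow-up carry no such limit, and the net benefit is reported over a range of willingness-to-pay values, not as a yes or no.
- *Effects on welfare and care costs cannot be seen at 6 months.* Some sick leave and care use can occur within that time, and the Societal implications section sets no time frame. Introduction 2.2.1 also names 6 months among the periods of interest.

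**Conclusion.** The point holds in limited form. For the net-benefit analysis and its acceptability curves, 6 months is the only horizon fixed, and it is fixed for costs alone. All treatment cost lies inside it, while any lasting QALY gain and cost offsets beyond it are left out. The share of the 24-month QALY gain captured runs from about 22% (no decay) to 69% (3-month half-life), under assumed exponential decay from month 1 and 3% discounting. Cost offsets are not quantified, because the protocol gives no cost figures. How much the horizon matters therefore depends on persistence, which the planned 12- and 24-month visits would measure. The undated effect term and the open ICER follow-up need settling whatever the persistence turns out to be.

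**What to change.** - Keep the 6-month analysis as the short-term analysis aligned with the primary endpoint.
- State one common horizon for costs and effects in both the ICER and the net benefit. For the EQ-5D version, define the effect as QALYs accumulated over that horizon.
- Prespecify the same ICER, net-benefit regression and acceptability curves at 12 and 24 months, from the EQ-5D and CAPS visits and register costs already planned, with costs and QALYs discounted after year one at a stated rate.
- Report every horizon and limit any conclusion drawn at 6 months to the short term. If the horizons disagree, present that as evidence on persistence; do not choose one of them afterwards.
- State how missing EQ-5D data at the later visits will be handled.

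No new visit or data source is needed. The costs are two further runs of the same analysis, a later final economic report if register data lag, and more missing EQ-5D data at 12 and 24 months than at 6.

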**1. IS TF-CBT AN EFFECTIVE TREATMENT IN PREVENTING THE DEVELOPMENT OF PTSD SYMPTOMS?**

1.1 OVERALL DESIGN AND PROCEDURE

The design is a randomized controlled trial, where patients in the emergency department who have experienced a traumatic event according to the A-criteria in the DSM-5 (e.g. car crash, rape), are randomized to receive either TF-CBT or to placebo. The placebo group will receive basic written information about PTSD and how treat these symptoms. Thus, the rationale for the placebo arm is to provide the patient with a sham treatment to rule out any major placebo effects. Given the estimated effect sizes in the previous trial by Rothbaum et al. we would need 352 patients (176 in each group) in order to detect a standardized effect size (Cohen´s *d*) of 0.3 (*p* = .05, 80% power). We also want to include additional 10 participants in the beginning of the trial just to test the study procedures.

Exclusion criteria are the following: a) Do not want to participate in the study, b) Ongoing intoxication (e.g. due to alcohol), c) Low cognitive capacity, d) Other serious psychiatric comorbidity (ongoing psychotic symptoms or symptoms from bipolar 1, suicidal ideation)

We will screen all trauma patients at Traumacentrum Karolinska (about 1500 patients per year). Psychiatric interviews will be conducted by a licensed psychologist at the emergency department or any related clinic (e.g. if the patient has been transferred to another clinic). Patients who fulfill the A-criterion in DSM-5 (i.e. they have experienced a highly stressful event threatening physical or psychological integrity) will be asked to participate in the study. Informed consent will be delivered both as written text as well as explained by the study personnel. Baseline assessments (shown below) will then be conducted.

After the patients have signed the informed consent and completed the baseline assessments, they are randomized to either TF-CBT or placebo. Block randomization will be done beforehand by an independent party (Karolinska Trial Alliance; KTA) on an 1:1 ratio.

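### The net-benefit analysis handles baseline only by subtraction and names no baseline covariate; run as written, the arm contrast is unbiased but less precise than it need be

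*Protocol*

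**What the plan says.** Protocol, Methods 2.3, defines individual net benefit as willingness to pay times effect, minus cost change.

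- Effect term: "E is the efficacy (i.e. PTSD status or gain on the EQ-5D". The first option is a status at follow-up; the second is read here as follow-up minus baseline.
- Cost term: it "is the cost change from baseline to primary endpoint (6-months". The numerator of the incremental cost-effectiveness ratio is formed in the same way: it "is the difference in cost change (from pre- to follow-up) between the two treatment groups".
- Comparison of arms: "a regression model with non-parametric bootstrapping (one thousand replications) to estimate be difference between TF-CBT treatment-as-usual", repeated over different willingness-to-pay values and shown as acceptability curves. No covariate is named and none is excluded.

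Methods 1.1 has CAPS, the Posttraumatic Diagnostic Scale, MADRS-S, EQ-5D and the side-effect form assessed "at baseline (i.e. before treatment allocation), 2-, 6-, 12-, 24-, 48- and 120 months using blinded assessors". Baseline EQ-5D and CAPS are therefore available before randomisation. Costs come from registers (Methods 2.1), for which no baseline look-back window is given.

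**The concern.** A change score removes the whole baseline value, as if the regression slope of follow-up on baseline were one. When the correlation is modest, this takes off too much and adds baseline noise to the outcome. Using baseline as a covariate removes only the part that predicts follow-up.

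A modest correlation is plausible here. Baseline is taken before an intervention that Methods 1.1 places within 72 hours of the accident, and Introduction 2.2.1 expects a sizeable share of patients to recover spontaneously. EQ-5D soon after acute injury may say little about EQ-5D at six months. This is an inference; the protocol gives no correlation.

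Cost-effectiveness is one of the three research questions (Introduction 4.1), and the acceptability curve is read from this one arm contrast. What is at stake is the width of its interval and how flat the curve is.

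**Working it through.** **The plan's own figure.** Methods 1.1 states "we would need 352 patients (176 in each group) in order to detect a standardized effect size" (Cohen's d) "of 0.3 (*p* = .05, 80% power". The normal approximation gives 175 per arm (350). The exact two-sided t calculation gives 176 per arm (352), with power 80.1%. The figure reproduces, but it does not bear on net benefit, for which the protocol states no precision.

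**Can adjustment lose precision?** Let s0 and s1 be the baseline and follow-up SDs and r their correlation.

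- Change score variance: s0² + s1² − 2·r·s0·s1
- Baseline-adjusted variance: s1²(1 − r²)
- Difference: (s0 − r·s1)², which is never negative

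In large samples adjustment therefore cannot be worse, whatever the SDs.

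**EQ-5D gain alone, equal SDs.** The variances are 2(1 − r)s² and (1 − r²)s², with ratio 2/(1 + r): 1.67 at r = 0.2 and 1.33 at r = 0.5. This is a ceiling that ignores cost.

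**EQ-5D gain within net benefit.** Let the effect term be a share f of net-benefit variance and treat cost as independent noise. Adjustment multiplies the effect part by (1 + r)/2, so the adjusted variance is (1 − f) + f(1 + r)/2 = 1 − f(1 − r)/2 of the unadjusted. The ratio of unadjusted to adjusted is 2/(2 − f(1 − r)).

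| f | r | Calculation | Variance ratio | SE ratio |
|---|---|---|---|---|
| 0.7 | 0.2 | 2/1.44 | 1.39 | 1.18 |
| 0.7 | 0.5 | 2/1.65 | 1.21 | 1.10 |
| 0.4 | 0.2 | 2/1.68 | 1.19 | 1.09 |
| 0.4 | 0.5 | 2/1.80 | 1.11 | 1.05 |
| 0.7 | 0.8 | 2/1.86 | 1.08 | 1.04 |
| 0.4 | 0.8 | 2/1.92 | 1.04 | 1.02 |

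For r of 0.2 to 0.5, the 352 patients carry the precision of about 352/1.39 = 253 to 352/1.11 = 317 patients analysed with adjustment.

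**If baseline cost helps too.** The table gives no credit for adjusting the cost change. A simulation with 176 per arm, cost change and EQ-5D gain equally weighted and both baselines as covariates gave SE ratios of 1.28, 1.15 and 1.06 at correlations of 0.2, 0.5 and 0.8. Theory gives 1.29, 1.15 and 1.05. This assumes equal SDs for baseline and follow-up cost, which the protocol does not support, so the table is kept as the main estimate.

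**PTSD status.** The effect term is not a change score, so there is no over-correction in it. With r now the correlation of the baseline covariate with later status, the gain in that term is 1/(1 − r²): 1.04 at r = 0.2 and 1.33 at r = 0.5, before dilution by cost. The cost term is still a change.

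**Chance baseline difference.** One standard error is √(2/176) = 0.107 SD. A difference b moves the unadjusted gain contrast by −(1 − r)b, in size 0.085 SD at r = 0.2, 0.053 at 0.5 and 0.021 at 0.8. Averaged over randomisations the shift is zero.

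**The case against.** The strongest objection is that the protocol never says the regression is unadjusted. It names no covariates and excludes none, and a statistical analysis plan that is not shown may list them. That stands: an arm-only model is inferred from silence. Nothing in the formula blocks adjustment either. With baseline EQ-5D and baseline cost in the model, the arm coefficient is the same whether the outcome is the change-based net benefit or its follow-up version. What remains is that the protocol itself fixes the change-score terms and states no other use of baseline.

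Four stronger readings are tempting and not supported:

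- A reader might infer that baseline data go unused. They are used: both the cost change and the EQ-5D gain subtract baseline.
- A reader might infer bias from chance imbalance. The contrast is unbiased, and the bootstrap interval already reflects this variation. Scaling the shift against d = 0.3 would also mislead, because the protocol does not tie that effect to EQ-5D.
- A reader might take 1.67 to 1.33 as the loss. Those ratios leave out cost, which is always part of net benefit.
- A reader might extend over-correction to every effect term. It does not apply to PTSD status, which is also the only clinical outcome named for the cost-effectiveness ratio.

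It is also fair to say that baseline cost is not a ready-made covariate: it is absent from the baseline list in Methods 1.1, and its register window is undefined.

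**Conclusion.** The point holds as a modest, avoidable loss of precision. If the analysis is run as Methods 2.3 describes it, the EQ-5D-gain version has about 1.1 to 1.4 times the variance of the baseline-adjusted version. Its intervals are about 5% to 18% wider and its acceptability curve correspondingly flatter.

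That range rests on assumptions, since the protocol gives none of the inputs: equal SDs at baseline and six months, correlation 0.2 to 0.5, effect share 40% to 70%, and cost as independent noise. At a correlation of 0.8 the SE loss is only 2% to 4%. The documents do not show that the result would be biased or that the final model will certainly omit covariates.

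**What to change.** In Methods 2.3, or in the analysis plan before any results are seen, state the following:

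- At each willingness-to-pay value, net benefit is regressed on arm, baseline EQ-5D and baseline cost, with baseline CAPS added when the effect is PTSD status.
- Baseline cost is the same pre-period register cost that already forms the cost change, and its look-back window is given.
- The adjusted model is refitted in each of the one thousand bootstrap replicates, and the acceptability curve is read from the adjusted arm coefficient.
- The unadjusted result is shown as a sensitivity analysis.

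The cost is a few lines of text, a little more analysis work and a decision on the look-back window. EQ-5D and CAPS are already measured before allocation, and a baseline cost is already needed for the cost change, so no new patient assessment is required. Naming the covariates in advance also prevents their being chosen after the curves have been seen.
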